## Abstract

**Background:**

Cocaine use has increased in most European countries, including Switzerland, and many states worldwide. The international literature has described treatment models that target the general population. In addition to supplying informative measures at the level of primary and secondary prevention, the literature also offers web-based self-help tools for problematic substance users, which is in line with tertiary prevention. Such programs, however, have been primarily tested on individuals with problematic alcohol and cannabis consumption, but not on cocaine-dependent individuals.

**Methods/Design:**

This paper presents the protocol of a randomised clinical trial to test the effectiveness of a web-based self-help therapy to reduce cocaine use in problematic cocaine users. The primary outcome is severity of cocaine dependence. Secondary outcome measures include cocaine craving, consumption of cocaine and other substances of abuse in the past month, and changes in depression characteristics. The therapy group will receive a 6-week self-help therapy to reduce cocaine consumption based on methods of Cognitive Behavioural Therapy, principles of Motivational Interviewing and self-control practices. The control group will be presented weekly psycho-educative information with a quiz. The predictive validity of participant characteristics on treatment retention and outcome will be explored.

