To assess the effectiveness of the Snow Control therapy, an appropriate psycho-educative online control condition was developed. Participants in the control condition receive eight psycho-educative information modules on the risks, potential harms and other important information about cocaine consumption. The frequency of the control condition is comparable to the 6 weeks of intervention; however, it does not include the presentation of a consumption diary first. After having read each of the information modules, the participants are invited to participate in a weekly quiz to evaluate their information knowledge.

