### Hypotheses

We hypothesise that Snow Control participants in the therapy group will show higher reductions on the Severity of Dependence Scale (SDS) [20] sum score and cocaine consumption than those in the control group at the 6-week treatment termination and at the 6-month follow up. Moreover, we expect participants in the therapy group to improve more significantly with respect to the secondary outcomes between baseline and 6-week treatment termination. We also expect the participants in the therapy group to show significantly higher retention.

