### Measurement instruments

The primary outcome instrument, the Severity of Dependence Scale (SDS), is a 5-item questionnaire that indicates the severity of dependence on cocaine. Each of the five items is scored on a 4-point scale (0-3). The total score is obtained through the addition of the 5 item ratings. High scores indicate a high level of dependency.

Moreover, the following secondary outcome instruments will be applied: 1) The Cocaine Craving Questionnaire Brief CCQ-B [21] is a short (10 items) and validated instrument that was derived from the CCQ-Now [22] (45 items). It contains 10 craving symptoms that are rated on a 7-point Likert scale from strongly agree to strongly disagree. 2) The "Fragebogen Substanzanamnese" (FDA) ascertains the years of lifetime consumption, the past month's consumption, and the way of consumption for the DSM-IV/ICD-10 substances of abuse. This measure was derived from the EuropeASI [23]. 3) The short version of the Beck Depression Inventory (BDI-V) [24] is a derived, validated, and user-friendly short version of the classical Beck Depression Inventory. The BDI-V contains 20 items with a 6-point Likert scale (0/never-1-2-3-4-5/almost every time). Accordingly, the values range from 0 to 100, with a cut-off of 45 for a serious depressive episode that requires further treatment.

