### Randomisation and Allocation

Once participants have completed their baseline assessment, they will be randomly brought to part 1 of either the intervention or the control tool, and this assignment will be automatically registered in the background database. This assignment will also be registered in their Internet browser as a cookie to avoid multiple registrations by one person. If a person returns to the Snow Control start page and attempts to register for a second time, she or he will be recognised by the background database and automatically be redirected to his or her allocation.

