### Trial Flow

Figure 1 provides an overview of the trial flow. If a participant successfully completes the baseline assessment (t0), he or she will be introduced step-by-step into either the intervention or the control tool (part 1) and invited to participate in module 1. Every week and two days in advance to the next module, a participant will receive an automated e-mail notification to login and return to the next module. Modules 1 to 4 will be accessible only week by week. After three weeks, the automated e-mail will direct the participant to the intermediate assessment (t1) before he or she has access to module 4 of the intervention or the control tool (end of part 2). Six weeks after the baseline assessment, completion of the additional optional modules of part 3 and weekly reminder e-mail notifications, participants will be invited again by e-mail to login and complete the final study assessment (t2). It is possible that some participants will wish to continue with some of the modules in part 3 after this period. However, the decision has been made to have the follow up timing depend solely on the time interval since t0. In our opinion, this is the best possible adherence to the 'intention to treat' principle. For the follow up assessment (t3), participants will be invited by an e-mail message 6 months past t0, with the notification that completion of the entire 6-month follow up assessment will be compensated by a 40 Euro incentive (an online voucher or an online charitable donation).

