### Handling of study dropouts

Each week, participants will be sent an automated e-mail that contains a reminder to work on the next module and a direct link to the Snow Control login site. If participants do not log in, they will receive a reminder e-mail every three days within the following two weeks. If they do not continue their participation after these reminders, they will be considered to have dropped out of the study. Participants who skip one of the study questionnaires by not answering all of the questions will be identified in the data analyses and counted as dropout (cut-off: answered at least 70% of the questions).

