### Data Analysis

Data will be analysed according to the intention-to-treat principle. Multiple imputations of missing data handling procedures will be implemented using the statistical software package STATA (version 10). Baseline measurements will be compared using t- and Chi-squared tests. Differences between primary and secondary outcome variables at three and six weeks will be tested using a repeated measures ANOVA. Effect sizes will be calculated using Cohen's d [27]. Differences in treatment retention will be tested using multiple logistic regression analyses. We will additionally conduct explorative regression analyses in order to test whether baseline variables predict cocaine abstinence, cocaine craving (CCQ-B), or reduced symptoms of depression (BDI-V). For these analyses, we will use linear, multinomial, or binary regression models dependent on the scale level of the outcome measures.

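### The 3-week past-month consumption measure reaches back before randomisation, so its arm comparison is attenuated (about 9 of 30 days when completed on day 21)

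*Protocol article*

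**What the plan says.** All references are to the protocol article.

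- **Outcome and instrument.** The Abstract names "consumption of cocaine and other substances of abuse in the past month" among the secondary outcomes, and the aims repeat it. Under Measurement instruments, the FDA "ascertains the years of lifetime consumption, the past month's consumption, and the way of consumption".
- **Schedule.** Table 2 marks the FDA at baseline, 3 weeks, 6 weeks and 6 months. It gives no different recall period for the 3-week visit.
- **Timing.** The section Randomisation and Allocation fixes when this happens: "Once participants have completed their baseline assessment, they will be randomly brought to part 1 of either the intervention or the control tool". Trial Flow places the intermediate assessment (t1) three weeks later, before module 4 opens.
- **Late completion.** Under Handling of study dropouts, for participants who do not log in: "they will receive a reminder e-mail every three days within the following two weeks".
- **Analysis.** Data Analysis states: "Differences between primary and secondary outcome variables at three and six weeks will be tested using a repeated measures ANOVA". In context this means differences between the arms.
- **Hypotheses.** Therapy participants are expected to reduce their SDS score and their cocaine consumption more "than those in the control group at the 6-week treatment termination and at the 6-month follow up". Three weeks is not named.
- **Other consumption data.** The therapy arm keeps a 7-day diary. Of the control condition the Background says that "it does not include the presentation of a consumption diary first".

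**The concern.** The recall period, the visit and the test are each stated, and together they do not fit. Three weeks after randomisation, a past-month question still covers days on which nobody had been allocated. Treatment cannot have changed use on those days, and the baseline FDA has already counted them.

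This pulls the 3-week arm difference in consumption towards no difference, and a larger sample does not remove the pull. It also bends the time course: a treatment effect that was the same at weeks 3 and 6 would seem to grow between them, because the first reading is diluted and the second is not. A repeated measures analysis is meant to describe that pattern. No other consumption measure common to both arms could replace the FDA at week 3, since the control arm is not led through the diary.

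**Working it through.** The article gives no figure for this point, so there is none to reproduce.

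**Inputs**
- Recall window W: one month. I take 30 days, because Table 1 counts recent use over 30 days, and show 28 and 31 as the range.
- Randomisation: day 0, directly after baseline.
- Completion of t1: day d = 21 if on schedule. Two weeks of reminders allow completion up to about day 21 + 14 = 35.

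**Step 1: share of the window before randomisation**

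Share = max(0, W − d) / W, and the retained part is 1 − share.

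| W (days) | d (day) | Days before randomisation | Share | Retained |
|---|---|---|---|---|
| 28 | 21 | 7 | 25% | 75% |
| 30 | 21 | 9 | 30% | 70% |
| 31 | 21 | 10 | 32% | 68% |
| 30 | 24 | 6 | 20% | 80% |
| 30 | 28 | 2 | 7% | 93% |
| 30 | 30 or later | 0 | 0% | 100% |

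At 6 weeks (d = 42) the 30-day window runs from day 12 to day 42, so the share is 0%. At 6 months it is also 0%.

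**Step 2: effect on the 3-week arm difference**

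Randomisation makes expected use before day 0 equal in the two arms. Let Δ be the mean daily difference between arms from day 0 to day d. The arm difference per day of window is then (d × Δ + (W − d) × 0) / W = (d/W) × Δ. On schedule this is 21/30 × Δ = 0.70 Δ. The result does not need a constant effect, because Δ is an average over the days since randomisation. As an illustration with evenly spread use, a true 40% reduction would show as 0.70 × 40% = 28%.

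**Step 3: what this could mean for power (illustration only)**

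The article gives no SD for consumption. Suppose an undiluted comparison had 80% power at two-sided 5%, and the SD stayed the same. The expected test statistic would fall from 1.96 + 0.84 = 2.80 to 0.7 × 2.80 = 1.96, which is about 50% power. The sample size needed would rise by 1/0.7² = 2.04. The SD need not stay the same, so this is less certain than Step 2.

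**Step 4: what passes into the ANOVA**

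The article does not say whether baseline is a level of the model or which term is the test. Three assumed cases show the spread:
- Equal-weight average of weeks 3 and 6, constant effect: (0.70 + 1)/2 = 0.85, a 15% loss.
- The same average, with the true week-3 effect half the week-6 effect: (0.35 + 1)/(0.5 + 1) = 0.90, a 10% loss.
- Group-by-time test with baseline as a level, constant effect, equal variances and sphericity: the pattern (0, 1, 1) becomes (0, 0.7, 1). The sum of squares about the mean falls from 0.667 to 0.527, and √(0.527/0.667) = 0.89, an 11% loss.

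These are examples, not estimates for this trial.

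**The case against.** The strongest reply is that no stated consumption hypothesis depends on week 3. The hypotheses name 6 weeks and 6 months, where the window lies wholly after randomisation, and t1 is only an intermediate reading of a secondary outcome. The error is also conservative, and it disappears for anyone who completes t1 on day 30 or later. All of this stands, and it limits how much the point matters. It does not remove the point, because Data Analysis still commits to testing secondary outcomes at three weeks and nothing in the article shortens the recall there. Late completion also makes the dilution vary between participants, and between arms if completion times differ.

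A reader might infer more than the documents support:
- **That 30% of every 3-week window is lost.** It is the day-21 value for a 30-day month.
- **That the repeated measures result loses a fixed 15%.** This needs equal averaging of weeks 3 and 6 and a constant effect from day 0. The article states neither, and its modules open week by week.
- **That abstinence is misclassified at a 3-week endpoint.** Someone who stopped on day 0 could indeed still report past-month use at t1. But no 3-week abstinence endpoint is defined; abstinence appears only in the exploratory regressions, without a time point.
- **That the overlap of the 3- and 6-week windows is a further bias.** They share days 12 to 21, which is 9 days, all after randomisation. This adds correlation between repeated measures and does not bias the arm comparison.

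**Conclusion.** The point holds, with limited scope. For a participant who completes t1 on day 21, about 9 of 30 days (25% to 32% across month lengths) precede randomisation, and the 3-week arm difference in consumption is attenuated to about 70% (68% to 75%) of the mean daily difference since randomisation. This rests on the past-month wording applying at week 3, as Table 2 implies, and on arms that are equal in expectation before day 0. Completion after day 21 makes the attenuation smaller.

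Some of the distortion enters any repeated measures ANOVA that includes week 3. Its size there cannot be fixed from the article, because it depends on the model and on the onset of effect.

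It would be wrong to conclude that the trial's main results are compromised. The SDS is a separate instrument for which the article gives no past-month window, and the hypothesised consumption comparisons at 6 weeks and 6 months are clean. This is a correction worth making to a stated test of a secondary outcome.

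**What to change.** **Preferred.** In Data Analysis, take 3-week FDA consumption out of the between-arm test and report it descriptively. Test consumption at 6 weeks and 6 months, as the hypotheses already state. The sentence quoted above names only three and six weeks, so the revision should name 6 months for consumption. The cost is one sentence and the loss of a formal 3-week consumption test that no hypothesis calls for.

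**Alternative.** Keep the 3-week test, but at t1 ask about use since baseline and analyse it as a daily rate. The share from before randomisation is then 0%, whatever the day of completion. The cost is one recall phrase in an online questionnaire. The small downside is that the recall window differs from the other visits, and converting to a daily rate does not remove differences in how well people recall over different periods. It also needs the FDA item to give a quantity that can be divided by days, and the article does not state its unit.

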**Discussion:**

To the best of our knowledge, this will be the first randomised clinical trial to test the effectiveness of online self-help therapy to reduce or abstain from cocaine use. It will also investigate predictors of outcome and retention. This trial is registered at Current Controlled Trials and is traceable as NTR-ISRCTN93702927.

## Background

Although data on the prevalence of problematic cocaine use and addiction are lacking in Switzerland and many other developed countries, there is no doubt that, in line with other countries, cocaine use has increased in Switzerland in recent years [1,2]. Over the past ten years, the number of cocaine-related disorder treatments has quintupled in outpatient treatment and advisory services [2]. In 2005, resident institutions reported that, for the first time in history, cocaine outstripped opiates as the main substance used [3]. This trend has also been observed in outpatient units [3]. Further evidence of increased cocaine consumption has been found by quantifying cocaine concentrations in sewage effluents [4] and in recent HBSC student surveys [5]. The abovementioned increase in treatment requests likely reflects only a minority of cocaine users. Presumably, the majority of users consume cocaine on a quasi-controlled basis, whereas only a small fraction of consumers is likely to take advantage of available treatments [6]. However, it is expected that some users will switch from controlled to problematic use [7]. For those users, interventions that follow the principle of concurrent cover (i.e., non-invasive, low-cost interventions in which therapeutic intensity can be enhanced according to need) appear appropriate.

In recent times, the international literature has described treatment models that target the general population. In addition to supplying informative measures at the level of primary and secondary prevention, the literature also offers web-based self-help tools for problematic substance users, which is in line with tertiary prevention [8-10].

Web-based self-help programs that reduce problematic consumption are able to reach "hidden" consumer groups in the general population due to their low treatment threshold and non-restrictive setting for intervention [11]. Furthermore, these programs show a remarkably positive cost-benefit relation [12], which is of interest in Switzerland and other industrialised countries suffering from exorbitant health costs. Such programs, however, have been primarily tested on individuals with problematic alcohol and cannabis consumption but not on cocaine-dependent individuals [9,10,13].

Therefore, Snow Control, a six-week self-help therapy for problematic cocaine users who intend to reduce or stop consuming and have access to the Internet was developed in 2010. Snow Control is based on methods of Cognitive Behavioural Therapy (CBT) that have been tested on cocaine addicts [14,15], principles of Motivational Interviewing [16], current self-control practices and the established Relapse-Prevention Model [17-19].

The therapy is structured into three parts and includes the following eight modules that are activated for access week by week (modules 1 to 4) and four additional voluntary modules (module 5 to 8) that can be activated during week 4-6:

• Part 1: Introduction

○ Registration process

○ Explanation of the cocaine consumption diary and its fully automated progress charts and statistics

○ Examination of the pros and cons resulting from a change in cocaine consumption patterns to address motivation

○ Explanation of the "My Snow Control" folder (This folder allows individuals to review the acquired summarised module documents, e.g., the list of the top five strategies for dealing with cocaine cravings)

• Part 2: Key Modules (to be worked through in the following order)

○ Module 1: Strategies for goal achievement

○ Module 2: Identifying risk situations

○ Module 3: Dealing with cocaine craving

○ Module 4: Dealing with relapses

• Part 3: Further Modules (to be worked through in optional order but with the recommendation to complete at least two)

○ Module 5: Enjoying leisure time

○ Module 6: Dealing with burdens

○ Module 7: Saying "no" to foster refusal skills

○ Module 8: Preserving achievements

After the completion of part 1, each login in the therapy group will direct the participant to the consumption diary. The participants are asked to determine the amount of cocaine they plan to consume in the next 7 days and to specify the amount of cocaine consumed in the past 7 days into their consumption diary. After the completion of the consumption diary, they are directed to their weekly module (part 2 to be worked through in the above mentioned order; part 3 to be worked through in an optional order).

To assess the effectiveness of the Snow Control therapy, an appropriate psycho-educative online control condition was developed. Participants in the control condition receive eight psycho-educative information modules on the risks, potential harms and other important information about cocaine consumption. The frequency of the control condition is comparable to the 6 weeks of intervention; however, it does not include the presentation of a consumption diary first. After having read each of the information modules, the participants are invited to participate in a weekly quiz to evaluate their information knowledge.

## Methods/Design

### Aims of the trial

This study aims to test the effectiveness of the web-based cognitive-behavioural self-help therapy Snow Control to reduce cocaine use in problematic cocaine users in a two-arm randomised controlled trial. The primary outcome is the change in severity of cocaine dependence between baseline, 3 and 6 weeks of therapy/intervention and at a 6-month follow up. The secondary outcome measures include changes in cocaine craving, the past month's consumption of cocaine and other substances of abuse and changes in depression characteristics. The predictive validity of participant characteristics for treatment retention and outcome will be explored.

### Study population

The study population will be recruited through the Snow Control website, several websites from local outpatient treatment centres and from nightlife prevention websites. In addition, advertisements in Internet-forums and newspapers will be traced.

### Hypotheses

We hypothesise that Snow Control participants in the therapy group will show higher reductions on the Severity of Dependence Scale (SDS) [20] sum score and cocaine consumption than those in the control group at the 6-week treatment termination and at the 6-month follow up. Moreover, we expect participants in the therapy group to improve more significantly with respect to the secondary outcomes between baseline and 6-week treatment termination. We also expect the participants in the therapy group to show significantly higher retention.

### Measurement instruments

The primary outcome instrument, the Severity of Dependence Scale (SDS), is a 5-item questionnaire that indicates the severity of dependence on cocaine. Each of the five items is scored on a 4-point scale (0-3). The total score is obtained through the addition of the 5 item ratings. High scores indicate a high level of dependency.

Moreover, the following secondary outcome instruments will be applied: 1) The Cocaine Craving Questionnaire Brief CCQ-B [21] is a short (10 items) and validated instrument that was derived from the CCQ-Now [22] (45 items). It contains 10 craving symptoms that are rated on a 7-point Likert scale from strongly agree to strongly disagree. 2) The "Fragebogen Substanzanamnese" (FDA) ascertains the years of lifetime consumption, the past month's consumption, and the way of consumption for the DSM-IV/ICD-10 substances of abuse. This measure was derived from the EuropeASI [23]. 3) The short version of the Beck Depression Inventory (BDI-V) [24] is a derived, validated, and user-friendly short version of the classical Beck Depression Inventory. The BDI-V contains 20 items with a 6-point Likert scale (0/never-1-2-3-4-5/almost every time). Accordingly, the values range from 0 to 100, with a cut-off of 45 for a serious depressive episode that requires further treatment.

